### Inclusion criteria

Patients who are 18 years and older, with HIV-1 infection and who are visiting selected outpatient clinics for their HIV care will be eligible for this study. Patients with hazardous alcohol use will be selected using the AUDIT questionnaire (hazardous drinkers score 8 to 19 for men and 7 to 19 for women).

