### Sample size calculation

The sample size was calculated using Open Epi
[29]. Based on the current AUDIT score of 12 among HIV patients, it is assumed that the intervention will reduce the current AUDIT score by 12% to 10.6
[30,31]. Based on this assumption, the estimated sample size will allow us with 80% power (5% level of significance) to detect the difference of 12% between the two groups. This will give a minimum of 99 patients per arm. It is expected that 20% of participants may be lost prior to completing the 3-month and 12-month follow-up assessments so that the final sample would be 120 per arm. A total of 240 HIV patients (with AUDIT scores 8 to 19 for men or 7 to 19 for women) will be recruited for the study.

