### Data analysis

Virological failure will be defined according to the definition in the South African national guidelines on HIV: a repeat HIV viral load ≥1,000 copies/ml after intense adherence assessment
[43]. Immunological failure will be defined according to the WHO definition: a fall of CD4 cell count to pre-therapy baseline (or below), or a 50% fall from the on-treatment peak value (if known), or a persistent CD4 cell count level below 100 cells/mm^3^[44].

Means, standard deviations, and percentages will be used for descriptive statistics. To examine differences between groups, the *t* test for continuous data and the chi-square test for categorical data will be used. Generalized linear model repeated measures 2×3 analysis of variance will be used for comparing observations (alcohol use score) across the three contact periods to demonstrate a treatment intervention×time interaction. To avoid possible bias from excluding patients with missing values, patterns of missing values will be analyzed. Multiple imputation methods using generalized estimating equating methods, based on all data available in the model, using five imputed datasets, will be used to impute missing data at all contact points (baseline and follow-up at 3 and 12 months). SPSS for Windows version 18.0 (SPSS, Inc., Chicago, IL, USA) will be used for calculations.

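### The alcohol score is tested by a 2×3 group-by-time interaction with baseline AUDIT as a response, but the stated 80% power fits a plain two-group comparison and is not shown to apply to that test

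*Protocol article*

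**What the plan says.** The sample size section starts from a mean: "Based on the current AUDIT score of 12 among HIV patients". It then sets the effect: "it is assumed that the intervention will reduce the current AUDIT score by 12% to 10.6". On that basis it claims "80% power (5% level of significance) to detect the difference of 12% between the two groups" and concludes: "This will give a minimum of 99 patients per arm". It states no SD, no correlation between visits and no time point for the difference. Enrolment is raised to 120 per arm for 20% loss.

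The data analysis section lists a t test for continuous data in general, without linking it to AUDIT or to a visit. The next sentence deals with the alcohol score: a repeated-measures 2×3 "analysis of variance will be used for comparing observations (alcohol use score) across the three contact periods", meant to show an intervention-by-time interaction. The same paragraph gives the contact points as baseline, 3 months and 12 months. Baseline AUDIT is thus one of the responses, and no baseline adjustment is described.

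Entry is restricted on the same scale: "hazardous drinkers score 8 to 19 for men and 7 to 19 for women".

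**The concern.** Two different tests are in play. A two-group comparison at one visit depends on the difference and the SD at that visit. The 2×3 interaction is a 2-degree-of-freedom test of whether the arm difference changes over three contacts. Because baseline is a response, the test works on departures from baseline, and its noise depends on the baseline SD and on the correlations between visits. A power figure for the first test does not carry over to the second.

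The hypothesis section predicts a larger reduction in drinking in the intervention arm, and the interaction is the test named to show it. If its power is below the figure quoted, the trial may miss the 1.4-point effect that it was sized for. A significant 2-df interaction also gives no estimate of the arm difference at 3 or 12 months, which the objectives ask for.

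**Working it through.** **Inputs.** From the sample size section: means 12 and 10.6 (difference 1.4), 80% power, 5% level (two-sided assumed), 99 per arm. Not in the article, hence assumed: the SD, the correlation r between visits, and how the effect evolves over time.

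**The plan's own figure.** With SD 3.5, n = 2 × (1.96 + 0.8416)² × (3.5/1.4)² = 98.1, i.e. 99 per arm, and the two-sample t test then has 80.0% power. Solving back from exactly 99 gives SD 3.52. So 99 fits a plain comparison of two means with standardized difference 1.4/3.5 = 0.40 and no correlation term. Only this ratio matters below.

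**Scenario A: SD 3.5 at every visit, equal correlation r, 99 per arm.**

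- Interaction: noncentrality = (n/2) × Σ(d_t − mean d)² / [SD²(1 − r)], with 2 and 2(2n − 2) df. For d = (0, 1.4, 1.4) the sum of squares is 1.307. At r = 0.3: 49.5 × 1.307 / (12.25 × 0.7) = 7.54, power 69%.
- Baseline-adjusted, one visit: residual variance SD²(1 − r²).
- Baseline-adjusted, mean of both follow-ups: residual variance SD²[(1 + r)/2 − r²]. At r = 0.3: 12.25 × 0.56 = 6.86, standard error √(2 × 6.86/99) = 0.372, ratio 1.4/0.372 = 3.76, power 96%.

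| r | Interaction | Adjusted, one visit | Adjusted, mean of both | Interaction, effect halved at 12 months | Adjusted mean, effect halved |
|---|---|---|---|---|---|
| 0.2 | 62% | 82% | 96% | 50% | 80% |
| 0.3 | 69% | 84% | 96% | 55% | 80% |
| 0.4 | 76% | 86% | 97% | 62% | 82% |
| 0.5 | 83% | 90% | 98% | 71% | 84% |
| 0.6 | 91% | 94% | 99% | 81% | 89% |

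For a sustained effect the interaction reaches 80% at r of about 0.46 (0.47 with the 96 per arm left after 20% loss from 120). If the effect halves by 12 months, it needs about 0.59 (0.60 with 96).

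**Scenario B: selection on AUDIT shrinks the baseline SD.** Suppose that visits correlate at r_u before selection, that selection halves the baseline SD (k = 0.5), and that the follow-up SD is 3.5. Follow-up variance is then 1 − r_u² + r_u²k² of its unselected value, and the slope of follow-up on baseline stays at r_u. For r_u = 0.6:

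- The factor is 0.73, the unselected variance 12.25/0.73 = 16.78, and the baseline SD 0.5 × √16.78 = 2.05. The correlation among those enrolled is 0.35.
- Change variance = 4.20 + 12.25 − 2 × 0.6 × 4.20 = 11.41, SD 3.38. Equal SDs at the same correlation would give 3.99.
- Covariance of the two follow-ups = 16.78 × (0.6 − 0.36 + 0.09) = 5.54. Covariance of the two changes = 5.54 − 5.03 + 4.20 = 4.70.
- Multivariate interaction test: noncentrality = 99 × 1.4² / (11.41 + 4.70) = 12.0, power 88%.
- Adjusted mean of follow-ups: residual variance (12.25 + 5.54)/2 − 0.36 × 4.20 = 7.38, standard error 0.386, ratio 3.63, power 95%.

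| r_u (r after selection) | Interaction | Adjusted, one visit | Adjusted, mean of both | Interaction, effect halved | Adjusted mean, effect halved |
|---|---|---|---|---|---|
| 0.6 (0.35) | 88% | 85% | 95% | 74% | 77% |
| 0.7 (0.44) | 91% | 88% | 96% | 79% | 80% |

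At r_u = 0.5 (0.28 after selection) and a sustained effect, the interaction has 86% and the adjusted mean 95% (94% with 96 per arm).

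**The case against.** **The trial is not shown to be underpowered.** A reader might argue that entry at AUDIT 7 or 8 to 19 lowers the baseline-to-follow-up correlation below 0.46, so that the interaction must fall short. The documents do not support this. Selection on baseline lowers the correlation by shrinking the baseline SD, and that also removes noise from the change scores. A restricted correlation cannot be read off a table that assumes equal SDs. Scenario B treats both together, and the interaction exceeds 80% for a sustained effect. This part of the objection stands in full.

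**Adjustment at a single visit is not always better.** A reader might infer from scenario A that it is. In scenario B it has 85–88% against 88–91% for the interaction. The advantage that remains belongs to the average over both follow-ups, and it is small there if the effect halves (77–80% against 74–79%).

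**The average is not best for every time course.** If the effect vanished entirely by 12 months, the interaction in scenario A would have the same power as for a sustained effect (76% at r = 0.4). The averaged difference would be 0.7 with standard error √(2 × 12.25 × 0.54/99) = 0.366, ratio 1.92, or about 48% power. The visit-specific differences should therefore be reported as well.

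**The t test could be the powered test.** It would match the sample size statement, with the interaction serving the objective about changes. But the article does not assign it to AUDIT or to a visit, and it would leave baseline unused.

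**Detail may sit in an analysis plan that is not shown.** That excuses silence on covariates. It does not cover the article's explicit choice of the interaction next to a power figure for another comparison.

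**Conclusion.** The point holds as a mismatch and as an available gain, not as a proven shortfall. The 80% fits a two-group difference of 1.4 points with SD about 3.5, and nothing in the article shows that it applies to the 2-df interaction named for the alcohol score. Depending on SDs and correlations that are not stated, the interaction has 62–91% with equal SDs (r = 0.2–0.6) and 86–91% if selection halves the baseline SD, for a sustained effect.

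Across these scenarios a baseline-adjusted arm effect averaged over both follow-ups has about 94–99% for a sustained effect, and it stays ahead of the interaction when the effect halves by 12 months. This rests on the back-solved standardized difference of 0.40, the assumed correlations, and an effect that does not disappear by 12 months. The change is worth making because the data are already being collected and the result is the between-arm estimate that the objectives call for.

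**What to change.** In the data analysis section, analyse AUDIT at 3 and 12 months in a linear mixed model with arm, visit, arm-by-visit, baseline AUDIT and baseline-by-visit as fixed effects, and unstructured covariance between the two follow-ups. Name the baseline-adjusted arm difference averaged over the two follow-ups as the main alcohol comparison. Report the arm difference with its 95% CI at each visit as supporting. Keep the 2×3 profile over the three contacts as description.

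In the sample size section, state that the 80% refers to a two-group difference of 1.4 points at one visit, give the SD that was used, and say that it does not refer to the interaction test.

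The cost is wording in two sections, with no new patients, visits or measurements. The article reports that recruitment was still under way, so the change could be made before follow-up outcomes are analysed.

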### Outcomes

The findings will be important in the public health setting. The AUDIT screening tool has been developed by the WHO and proved to be applicable in a wide range of settings and target groups, including HIV patients in South Africa. The brief intervention we propose was also developed by the WHO and was proven to be successful in different settings
[42]. This makes the intervention widely applicable in different settings and regions. However, the intervention was never tested among patients with HIV infection in South Africa, which this trial aims to do. If the intervention proves to be efficient, it could potentially be incorporated in the South African HIV care guidelines. The generalizability of the trial result may not be extended to other countries, however, where there might be different patterns of alcohol consumption and different cultural beliefs regarding alcohol use and medical care.

### Trial status

Patients are currently being recruited for the trial.

### Ethical and governance approval

Ethical approval was given by the Medunsa Research and Ethics Committee (Project number: MREC/H/165/2011: IR). The Tshwane Research Committee has provided approval for the study (Project number: 2011/46).

## Abbreviations

AIDS: acquired immune deficiency syndrome; ART: antiretroviral therapy; AUDIT: Alcohol Use Disorder Identification Test; HIV: human immunodeficiency syndrome; WHO: World Health Organization.
